## Abstract

**Objectives:**

Cultural variations complicate psychiatric care, especially for migrant children. Transcultural psychotherapy (TCP) is an original psychotherapeutic technique developed to address complex situations of resistant mental disorders in the context of migration. This research will aim to assess the efficacy, the acceptability, and describe the therapeutic processes of TCP for the treatment of depression in first or second generation of migration children and adolescents.

**Method:**

Mixed method study using a multicenter, Bayesian randomized clinical trial with blinded evaluation of the primary outcome. Two parallel groups of 40 children or adolescents from 6 to 20 years old and their family will be included. In the experimental group, patients will attend six sessions of transcultural therapy in addition to usual care.

**Results:**

The improved Clinical Global Impression scale scores at 6 months will be compared across groups. Qualitative analysis of families and therapists' interviews will allow to specify the therapeutic processes and acceptability of the therapy.

**Conclusion:**

The findings will encourage the development and routinization of TCP for second‐line use and its adaption as a first‐line technique in this population.

AbbreviationsCDRS‐RChildren's Depression Rating Scale‐RevisedCGIClinical Global ImpressionCNILCommission Nationale de l'Informatique et des Liberté (French and European General Data Protection Regulation)iCGIimproved Clinical Global ImpressionSDstandard deviationSTAI‐CState‐Trait Anxiety Inventory for ChildrenTCPtranscultural psychotherapy

## INTRODUCTION

1

Migrant children represent 9.4% (47.3 million) of the European population and come, for a large part, from low‐ and middle‐income countries. In France, one in three children born has at least one parent who comes from elsewhere and 17% of children under 18 are migrants (INSEE, 2016). This proportion continues to rise and as they may differ in physical appearance, language, religion, and culture from the nonmigrant population (Hernandez, 2010), psychiatric care of immigrated families constitutes a growing challenge in many Western societies (Ceri et al., 2017; Georgiades, Paksarian, Rudolph, & Merikangas, 2018).

In Europe, migrant children have been shown to exhibit a 5%–10% higher risk of internalizing problems in various studies (Belhadj Kouider, Koglin, & Petermann, 2014; Kirkcaldy, Furnham, & Siefen, 2011; Reijneveld, Harland, Brugman, Verhulst, & Verloove‐Vanhorick, 2005). First generation of migration children shows more symptoms of depression, anxiety, post‐traumatic stress, or other mental disorders linked to internalizing disorders (impairment in school functioning, sleep disturbance, or suicidal ideation) than nonmigrant children (Fazel, Reed, Panter‐Brick, & Stein, 2012; Gaber et al., 2013; Jaycox et al., 2002). In recent studies, lifetime prevalence of most mental disorders was around 35% higher among second‐generation migrant children than among natives (Ceri et al., 2017). They showed particularly high rates of depression, anxiety, and post‐traumatic stress disorder which may lay on particular psychological vulnerabilities in migrant children (Chau, Baumann, Kabuth, & Chau, 2012; Kwak, 2003; Smokowski & Bacallao, 2007; Stevens & Vollebergh, 2008).

Treatment of depressive disorders in migrant children is a real challenge. Indeed, they are known to exhibit specific symptoms which may hinder the diagnosis and that cultural variations affect symptoms and clinical presentation of the entire range of mental health problems (Baker, 2001; Choi, 2002; Nguyen, Huang, Arganza, & Liao, 2007). Access to mental health services is also known to be more difficult for migrant children, particularly when they present symptoms of internalizing disorders that are more difficult to identify for caregivers (Leong & Lau, 2001; Nadeau, Jaimes, Johnson‐Lafleur, & Rousseau, 2017). Moreover, being part of an ethnic minority is known as a main risk factor of treatment dropout in youth mental healthcare (de Haan, Boon, de Jong, & Vermeiren, 2018).

As shown by the numerous cultural adaptations of research and therapeutic settings done over the world, culture has always been a concern in psychiatry (Kirmayer & Minas, 2000). Many care settings are currently designated to treat migrant families in America, Europe, or Australia, mostly based on the host country's migration patterns and citizenship model. Transcultural psychotherapy (TCP) is an original psychotherapeutic technique developed to meet specific requirements of migrants suffering from mental health issues. Its theoretical and methodological foundations rest on Devereux's (1967) work in ethnopsychiatry, and Nathan (1986) developed a psychotherapeutic technique intended to first‐generation migrants. Then, Moro (1998) adapted this technique to second‐generation which is now fully formalized as a second‐line treatment after failure of standard care. It combines cultural mediation techniques with elements from psychoanalytic parent–infant therapy, narrative therapy, and systemic and psychoanalytic family therapy (Sturm, Heidenreich, & Moro, 2009). Currently commonly used in France and in various European and American countries, TCP has shown its value in different contexts—first‐ or second‐generation migrants, refugees, unaccompanied minors, and so on—in numerous qualitative studies and clinical case reports (Moro, 2003, 2014; Sturm, Nadig, & Moro, 2011). However, it has never been evaluated using a design providing a high level of evidence, such as a randomized controlled trial.

In practice, the standard psychotherapeutic care offered to children and adolescents with depression does not usually lead to complete remission in migrant patients (de Haan, Boon, de Jong, Hoeve, & Vermeiren, 2013). These patients often present complex clinical depression with numerous comorbidities and require long care, with a substantial increase in human and financial resources, resulting in longer states of depression, which often become chronic (de Haan et al., 2013). We hypothesize that, when remission is not complete after 6 months of standard care, TCP is more effective to treat depression in migrant children and more acceptable for migrant families than the continuation of the standard psychotherapeutic care.

In this study, we present the study protocol of the randomized controlled trial we planned to evaluate TCP in migrant children using mixed methods and Bayesian approaches. Quantitative data will allow us to evaluate the efficacy of TCP using Bayesian inference which allows accounting for both a prior knowledge on the parameters to be determined as well as observations actually made on patients during the study. Qualitative aspects will help to specify the therapeutic processes to enhance the reproducibility and transmissibility: What are the principal therapeutic aspects during the group session? How to make them more effective? Finally, acceptability data will allow us to define the limits of its indications.

### Objectives

1.1

The main objective is to assess the efficacy of TCP to treat depression resistant to a first‐line therapy in first or second generation of migration children and adolescents, by comparing the percentage of patients in remission at 28 weeks after the start of TCP versus usual care (Figure 1). Secondary objectives consist in comparing the course of the severity of depression and of the level of depressive and anxiety symptoms in both groups over the first 34 weeks after inclusion, in evaluating the persistence of the efficacy of TCP at 1 year, and finally in describing the therapeutic processes that enabled the improvement of patients treated by TCP and the perceived efficacy and acceptability for the patient and the family.

**FIGURE 1 mpr1847-fig-0001:**
[figure not shown]
Chart of the conduct of the study

## METHOD

2

This is a multicenter, parallel group, Bayesian randomized clinical trial with blinded evaluation of the primary outcome and semi‐structured interviews for qualitative approach. The primary outcome—remission—will be assessed after the end of the follow‐up of the last included participant by three independent experts unaware of the received treatment who will watch the filmed semi‐structured clinical interview conducted by a psychologist at 34 weeks after inclusion (i.e., 28 weeks after the start of the TCP). The study was approved by the Research Ethics Board of Sud Mediterranean IV (CPP 19.10.01; January 13, 2020) and meet the requirements of the French and European General Data Protection Regulation (CNIL). The study is funded by a grant from Programme Hospitalier de Recherche Clinique—PHRC 2018 (French Ministry of Health)—and is registered on the website http://clinicaltrials.gov/ (NCT04206969).

### Population and sampling

2.1

Participants are recruited in six outpatient hospitals and psychological care centers in France in which every main therapist providing TCP has followed the same training. The study involves first and second generation of migrant children and adolescents suffering from depression resistant to a first‐line therapy, their families, and the therapists. The recruitment is planned to be from January 2020 to July 2022.

#### The child or adolescent and his/her family

2.1.1

Children and adolescents (the participants) referred to the transcultural consultation of one of the recruiting centers because they suffer from a depressive disorder resistant to standard management are eligible to be included in the study. TCP involves parents and siblings, so they are also present and active at each endpoint measure and involved in the semi‐structured interviews on acceptability of the therapy.

As mentioned above, the diagnosis of depressive disorders in migrant children and adolescent may be hindered by the effects of the culture (Haroz et al., 2017). To the well‐known important variability of depressive symptoms in childhood and adolescence (Birmaher et al., 1996) is added the extreme variability of symptoms in migrant youths (American Psychiatric Association, 2013, p. 167; Moro, 2009). For this reason, giving a full list of including and excluding symptoms is not possible. To improve the generalizability of our results, the depression diagnosis lays on gathering symptoms with a clinical global impression and an evaluation by the parents, but, to improve homogeneity, a nonexhaustive symptoms list is provided in Table 1 to help to do the diagnosis. Included participants must be aged 6–20 years old, be a first‐ or second‐generation migrant (born abroad or born from at least one parent who is born abroad), have a psychological and/or psychiatric follow‐up by a first‐line care, present a depression according the first‐line therapist based on usual as well as cultural symptoms criteria (Table 1), be rated at least “moderately ill” (score ≥ 4) on the severity scale of the improved Clinical Global Impression (iCGI) at inclusion, present transcultural issues confirmed by the referent (usual procedure of indirect preselection based on the presentation of the situation by referring physician), and have an informed consent signed by a legal tutor. Participants who have the following criteria cannot be included: patient or family who has previously had TCP, presents a severe mental disorder (e.g., excited delirium with great psychic disorganization and high suicidal risk) or somatic disease which may hinder the organization of the therapy, addressed for a legal expertize, refuses to participate.

**TABLE 1 mpr1847-tbl-0001:** List of potential depressive symptoms

Sadness
Diminish interest or pleasure in most of the usual activities
Insomnia or hypersomnia
Psychomotor agitation
Asthenia, loss of energy
Feeling of worthlessness or excessive guilt
Recurrent thoughts of death
School problems (school failure, drop in grades, aggressivity with adult, school refusal…)
Mutism and selective mutism
Runaways
Aggressivity
Impulsivity
Violence and delinquency
Conflicts with parents and adults from the community
Exclusion from family
Somatic pains
Massive separation anxiety
Regressive symptoms—loosing of an already acquired function such as speech, walk, stay alone for a sufficient time in relation to age, manage stress or anxiety for reasonable situations…
Denial of medical care for a chronic disease with no evident reasons
Cultural designation such as possessed by a spirit, being a child witch, or other cultural designations
State of trance

#### The first‐line therapist

2.1.2

Children and adolescents are referred to TCP consultations by a first‐line therapist who can work in a public hospital, a psychiatric and psychological center, in private practice, in a social or educational medical center. He is involved in individual semi‐structured interviews.

#### Therapists of the transcultural group

2.1.3

All the therapists involved in TCP sessions will be involved in focus group interviews.

### Treatment intervention, the TCP setting

2.2

TCP is a second‐line intervention. Physicians, psychologists, social worker, or child protection services refer patients to the transcultural consultation when they experience difficulties in building up a trustful relationship and good communication, when they feel helpless when confronted with cultural specificities of illness representation, or when they doubt about the pertinence of their diagnosis and the patient compliance with treatment and services. The evaluation of the referrals plays an important role. It may sometimes lead to an indirect consultation to help the professional who refer the patient to work in a more adequate way in their own consultation. When the TCP is proposed, the follow‐up should be provided by the initial care team who is invited to participate in the evaluation and to take part in the TCP.

This psychotherapy is composed of a 1‐hour session every 7 weeks. In these sessions, the patient and its family encounter a group of therapists of different cultural and linguistic backgrounds (psychiatry, psychology, anthropology, sociology, history, linguistics, or other scientific disciplines). The core family is invited with any member of the extended family or other people they feel close to. The group is a variable‐geometry setting which may vary from 2 to 10 participants, depending on the patient origin and the complexity of the situation. For example, a specific smaller group is designed to receive unaccompanied minors who could be intimidated with too many therapists. On the contrary, a bigger group is designed for receiving most of Sub‐Saharan African migrant families, as sickness is considered as a family and social concern and treated in the social group in many traditional societies. More information is provided in Appendix S1.

### Randomization

2.3

Participants are randomized with a 1:1 allocation ratio to “usual care and waiting list for TCP for at least 34 weeks” (control group) or “usual care and TCP beginning in the 6 following weeks” (experimental group). Every participant continues his/her usual treatment with the first‐line medical team throughout the duration of the study. As it is a pragmatic real‐life study, usual treatment may vary from one patient to another and from one first‐line medical team to another. It may include psychotherapy (individual, in group, or family therapy), medications, or institutional care (day‐hospital or inpatient care).

The randomization is centralized, stratified according to the recruitment center, with an unknown block size except from the statistician of the research center unit who generated this allocation sequence independently from the investigators and the statistician of the study. The allocation sequence was prepared using NQuery Advisor^®^ v7.0, validated software using pseudorandom numbers generator, and the randomization is performed electronically (IWRS) using the Cleanweb application (Télémédecine) software.

### Outcomes

2.4

#### Primary endpoint

2.4.1

The severity score on the iCGI is used to determine the remission of the depression (Kadouri, Corruble, & Falissard, 2007). The iCGI is an improved version of the Clinical Global Impression (CGI) scale frequently used in medical care and clinical research because of its face validity and practicability. The CGI scale has notably shown its interest in differentiating responders versus nonresponders in clinical trials in depression (Guelfi, 1990). The iCGI has been constructed to improve its content validity and reliability in depressive disorders by the use of a filmed semi‐structured interview and a blinded scoring with a new response format (Kadouri et al., 2007). It has been used in different diseases, with children and adolescents or in cross‐cultural comparisons (Bailey et al., 2015; Bourredjem et al., 2011; Marquer et al., 2015).

The iCGI was chosen as many specific scales that exist to measure childhood depression have shown their limit in transcultural contexts (Bhugra et al., 2014; Lu, Lindsey, Irsheid, & Nebbitt, 2017; Marquer et al., 2015). Moreover, depressive disorders in migrant children may be complex with cultural issues and many comorbidities. In this context, iCGI has two advantages as follows: it is not specific to a pathology or a cultural context and is adapted for the study as it lays on a filmed semi‐structured interview, which has already shown its benefit in the diagnosis of depressive disorders in children and adolescents with migration backgrounds (Ceri et al., 2017).

The primary endpoint is measured at 28 weeks after the start of TCP for the experimental group, before the fifth therapy session, which corresponds to the 34th week (W34) after inclusion as a 6‐week delay is needed to organize the first TCP session. In the control group, it is measured 34 weeks after inclusion.

This measure consists in a filmed semi‐structured clinical interview conducted by a psychologist trained in transcultural care, in the presence of an interpreter speaking the native language of the family. The interview guide has been constructed by specialists of transcultural care in childhood and adolescence (Appendix S2). It explores the severity of the symptoms in the past few weeks with the patient and the family. After the end of the follow‐up of the last included participant, three blinded independent experts will watch the film and rate the patient on a 7‐level scale: 1—normal, not at all ill; 2—borderline mentally ill; 3—mildly ill; 4—moderately ill; 5—markedly ill; 6—severely ill; and 7—among the most extremely ill patients. Remission is defined as a mean iCGI score over the 3 experts lower than 4.

#### Secondary endpoints

2.4.2

At each collection time points, the iCGI severity scale is used to measure the severity of depression, the Children's Depression Rating Scale‐Revised (CDRS‐R) is used to assess the level of depressive symptoms, and the State‐Trait Anxiety Inventory for Children (STAI‐C) is used to assess the level of anxiety symptoms (Spielberger, 1973).

The CDRS‐R is one of the most widely used rating scale for assessing severity of depression and change in depressive symptoms for clinical trials in children and adolescents (Mayes, Bernstein, Haley, Kennard, & Emslie, 2010). It's a 17‐item scale with answers on a 5‐ or 7‐point Likert scale depending on the item (total score ranges from 17 to 113). A score ≥40 indicates depression, whereas a score ≤28 is often used to define remission. This scale has shown good internal consistency and reliability for children over 6 years old (Poznanski & Mokros, 1996) as well as for adolescents (Mayes et al., 2010).

The STAI‐C is a self‐reported measure which has been widely used to assess state and trait anxiety of children and adolescents. It contains two scales of 20 items each, each subscale ranging from 20 to 60. The STAIC‐State scale is constructed to ask children how they feel at a particular moment in time. The STAIC‐Trait scale asks how they generally feel. Validity and reliability has been tested in many studies with children over 8 years old, adolescents and adults (Kirisci, Clark, & Moss, 1997).

Concerning the experimental group, a qualitative design is used to explore the therapeutic processes and the perceived efficacity and acceptability of the therapy. Sessions are transcribed verbatim and three semi‐structured interviews conducted by a psychologist after the fifth therapy session are organized with the family, the first‐line therapist and the transcultural group. The interviews' guides have been constructed by specialists of transcultural care in childhood and adolescence (Appendix S3).

### Study schedule

2.5

#### Screening time (indirect assessment without the patient)

2.5.1

The potential participants are referred to the different inclusion centers by a structured mail. A clinician evaluates the demand, the compatibility of the situation with the study, and contacts the family to propose an appointment with the research team in the next 5 weeks (Figure 1 and Table 2).

**TABLE 2 mpr1847-tbl-0002:** Assessment prevision for each research meeting

	Screening W −5 to −1	Baseline W0	Visit 1 W6 (±7 days)	Visit 2 W13 (±7 days)	Visit 3 W20 (±7 days)	Visit 4 W27 (±7 days)	Visit 5 W34 (±7 days)	Visit 6 W35–44* (±7 days)	Visit 7 W52* (±7 days)
Location of the meeting	‐	I	I or F or H	I or F or H	I or F or H	I or F or H	I	I or F or H	I
Information	✓	✓	‐	‐	‐	‐	‐	‐	‐
Written consent	‐	✓	‐	‐	‐	‐	‐	‐	‐
iCGI assessment	‐	✓	✓	✓	✓	✓	✓	‐	✓
CDRS‐R assessment	‐	✓	✓	✓	✓	✓	✓	‐	✓
STAI‐C assessment	‐	✓	✓	✓	✓	✓	✓	‐	✓
Qualitative interviews*	‐	‐	‐	‐	‐	‐	‐	✓	‐
Transcultural psychotherapy session*	‐	‐	✓	✓	✓	✓	✓	‐	‐

Abbreviations: CDRS‐R, Children's Depression Rating Scale‐Revised; F, first‐therapy center; H, family's home; I, inclusion center; iCGI, improved Clinical Global Impression; STAI‐C, State‐Trait Anxiety Inventory for Children; W, week.

*In the experimental group only.

#### Baseline visit and inclusion (week 0; duration: 1 h 30 min)

2.5.2

All the family members are invited to come in the recruitment center to meet a psychologist accompanied by an interpreter trained in transcultural care and briefed about the study. After information and general data gathering—questionnaire—the written consents (patient and family members, available in French on request) are collected, and the psychologist conducts a 5‐minute filmed semi‐structured interview with the participant and his/her family for the iCGI assessment.

For each participant fulfilling the inclusion criteria, randomization is then conducted. For each referred patient not included in the study, sociodemographic data and the reason for nonenrollment are collected.

#### Weeks 6–34—Intervention follow‐up visits (0 h 30 min)

2.5.3

Participants from both groups continue their usual care provided by the referent medical team outside the inclusion center.

In the experimental group, participants receive TCP in addition to usual care, which consists of five sessions every 7 weeks (W6, W13, W20, W27, and W34) ± 1 week. The verbatim of all therapy sessions is collected depending of each group habits: audio recording and full transcription or verbatim transcription during the therapy session, as well as details of each session (number of therapists and their profession).

In both groups, an assessment is conducted by a psychologist at W6, W13, W20, W27, and W34 (before the therapy session in experimental group). The same assessment process as at the baseline visit is performed.

#### Weeks 35–52—Free follow‐up

2.5.4

In the control group, TCP can be initiated or not, depending on clinical criteria. No new assessment will be performed after the W34 assessment. The research ends at W34 after the last measures for this group.

In the experimental group, TCP can be interrupted or continued depending on clinical criteria. Three qualitative semi‐structured interviews are organized between W34 and W44: one with the family (family interview); one with the therapists of the transcultural group (focus group); and one with the first‐line therapist(s) in charge of the participant who accompanied him during the therapy (individual or group interview depending on the case). These interviews explore the subjective experience of transcultural care, its acceptability, and the factors that each participant is highlighting as therapeutic in the TCP. The interviews are between 1 and 2 h long. At W52, a new assessment time is organized exactly in the same way as the previous follow‐up visits. The research ends at W52 after the last measures for this group.

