#### Secondary objectives

3.1.2

They will be analyzed using a frequentist perspective, but they will be considered as exploratory in nature. For this reason, no adjustment for multiple testing will be done. Score (iCGI, CDRS‐R, and STAIC‐State) change from baseline to W34 will be analyzed using a mixed‐effects model for repeated measures with treatment group, visit, and treatment group‐by‐visit interaction as fixed effects and the baseline score and center as covariates. The persistence of the efficacy of TCP over time will be evaluated using paired Student's *t*‐test comparing the mean of the score (iCGI, CDRS‐R, and STAI‐C‐State) at W34 and W52 in the experimental group.

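### The W34 to W52 comparison cannot show persistence of TCP efficacy: TCP continues after the W34 reading, optionally after session five, and the control arm is not measured after W34

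*Protocol article*

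**What the plan says.** All references are to the protocol article.

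- **Objective (1.1).** One secondary aim consists "in evaluating the persistence of the efficacy of TCP at 1 year".
- **Analysis (3.1.2).** "The persistence of the efficacy of TCP over time will be evaluated using paired Student's" *t*-test, comparing mean scores (iCGI, CDRS-R and the STAI-C state scale) "at W34 and W52 in the experimental group". No other analysis of persistence is given. The secondary objectives are labelled exploratory.
- **Planned TCP (2.5.3).** The experimental arm receives TCP "which consists of five sessions every 7 weeks (W6, W13, W20, W27, and W34) ± 1 week". Assessments at these visits take place "before the therapy session in experimental group".
- **Timing of W34 (2.4.1).** The primary endpoint section agrees: the reading is made "before the fifth therapy session, which corresponds to the 34th week (W34) after inclusion".
- **After W34 (2.5.4).** "In the experimental group, TCP can be interrupted or continued depending on clinical criteria". Control patients may start TCP and are not assessed again.
- **Usual care (2.3).** It continues in everyone throughout the study.

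**The concern.** A claim that efficacy persists is naturally read as saying that the benefit of a course of therapy is still there some time after the course has ended. To support that, the first reading should fall at or after the end of the course, the interval to the second should be free of the therapy (or exposure in it should be accounted for), and some comparison should show that the later state is due to the therapy.

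The plan secures none of the three. The first reading comes before a planned session. The interval allows further sessions, chosen on clinical grounds. The comparison arm has left the study by then. A stable mean at W52 could be a lasting effect, the effect of added sessions, the effect of continuing usual care, or natural course. A worse mean could be a lost effect in those who stopped, partly offset by patients who went on with TCP.

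At stake is a one-year durability statement. The article's discussion already looks ahead to routine use of TCP, so such a statement would probably be used.

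**Working it through.** The plan gives no figure that depends on this point, so there is nothing to reproduce. The check sets the schedule against the analysis, counts sessions, and gives two illustrations.

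**1. Exposure at the two readings**

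| | W34 reading | W52 reading |
|---|---|---|
| Sessions already received, by plan | W6, W13, W20, W27 = 4 | at least those plus W34 = 5 |
| TCP status | fifth session still to come | stopped or continued, on clinical grounds |
| Control arm measured | yes | no |

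- Minimum extra exposure: 5/4 = 1.25, or 25% more sessions than at the W34 reading. This needs only the planned fifth session.
- If the 7-week rhythm were kept up after W34, sessions would fall at W41 and W48, both before W52. The total would be 7, and 7/4 = 1.75, or 75% more. Section 2.5.4 sets no spacing, so this is a possible value under an assumption and not a planned one.
- The Abstract speaks of six sessions, while 2.5.3 and Table 2 schedule five. These passages must be reconciled, because the number affects how much TCP falls after the W34 reading.

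A patient who stops after session five has about 52 − 34 = 18 weeks without TCP before W52. A patient who continues may have little or none. The test in 3.1.2 pools both.

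**2. How pooling can hide the answer (assumed values)**

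Higher iCGI means more ill. Suppose that patients who stop worsen by 0.5 points, those who continue improve by 0.5, and a share q continue. Then

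mean change = (1 − q) × 0.5 − q × 0.5

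| q | Calculation | Mean change W34 to W52 |
|---|---|---|
| 0% | 0.500 − 0 | +0.50 |
| 25% | 0.375 − 0.125 | +0.25 |
| 50% | 0.250 − 0.250 | 0.00 |
| 75% | 0.125 − 0.375 | −0.25 |

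The same loss of effect in those who stop reads as worsening, stability or gain, depending only on q. The 0.5 values are invented. The table shows that the result is ambiguous, not how large any bias would be.

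**3. What the paired test could detect**

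With all 40 experimental patients measured (2.6), a two-sided paired *t*-test at 0.05 has 80% power only for a mean change of at least 0.45 SD of the differences. With 32 measured (assumed), this becomes 0.51 SD. A non-significant result would therefore not demonstrate stability, even if exposure were clean.

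**4. Comparison at W52**

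Control follow-up ends at W34. Even if every experimental patient stopped TCP after session five, a W34 to W52 change in one arm would describe a course and would not estimate efficacy at 1 year.

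**The case against.** The strongest reply is that the trial calls itself pragmatic and hides nothing. The article says that W34 precedes session five and that later TCP is a clinical decision, and it nowhere defines persistence as durability after a fixed course. On that reading, W52 shows whether benefit is maintained under a strategy that includes clinically guided continuation. This is a legitimate quantity, but it is not what the objective says. Adopting the reading means rewording the objective, which is the fix below. It also leaves the lack of a control measure untouched.

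Other parts of the reply stand and limit the point. A reader might infer four stronger things that the article does not support:

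- *That no patient has any time off TCP.* Those who stop after session five may have about 18 weeks. What is missing is an interval common to all, or one isolated in the analysis.
- *That the protocol regards W34 as the end of therapy.* It says the opposite about the schedule. At most this could be inferred from the word persistence.
- *That patients receive 75% more TCP by W52.* That needs a rhythm that 2.5.4 does not set.
- *That the bias has a known direction.* Who continues is described only as a clinical decision. That patients doing badly continue is plausible but not stated.

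It is also fair that session recording and descriptive tables may already be in the e-CRF or an analysis plan that is not shown. Their absence from the article is not the complaint. The complaint is that the objective, the two time points and the free-treatment rule, all fixed in the article, do not fit together.

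**Conclusion.** The point holds in this form. The W34 to W52 paired comparison cannot support a statement that TCP efficacy persists at 1 year. It starts from a reading taken during treatment, spans an interval with at least one further planned session and optional TCP after that, and has no control measure at its end. No choice of test changes this.

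The certain size is one extra planned session (five against four); anything above that depends on practice in free follow-up. Actual attendance is unknown, so the count is by plan. The bias in the score change cannot be sized from the article, and neither can its direction.

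The change is worth making, but its reach is limited: the objective is secondary and exploratory, and the W34 primary comparison is not affected. The W34 to W52 change remains usable as a description of patients allocated to TCP when further TCP is optional.

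**What to change.** 1. In 1.1 and 3.1.2, restate the objective and its analysis as the within-group change from W34 to W52 in patients allocated to TCP, with TCP stopped or continued during free follow-up. Do not claim persistence of efficacy.
2. State that the control arm is not measured after W34, so the W52 result is not an efficacy contrast. Report the change with its confidence interval, and do not read a non-significant test as stability.
3. Use the TCP sessions received from W34 (session five included) to W52, recording dates if they are not already captured, to show exposure after the W34 reading.
4. Report W52 scores separately for patients who stopped and patients who continued. Say that the split is clinically selected, rests on at most 40 patients and is descriptive. It does not remove the selection and cannot restore an efficacy claim.
5. Reconcile the six sessions in the Abstract with the five in 2.5.3 and Table 2.

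The cost is a rewording, session dates in the e-CRF and one extra table. Care, visits and sample size do not change. The price is a less favourable secondary claim.
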